#### Qualitative data

Staff (estimate n=50–70) involved in the delivery of services at the participating clinics will be invited to participate in focus groups three times during the trial, aligned with the stages of the trial (pre-implementation, implementation and post-implementation). Patients who attend one of the eight participating clinics as a new patient during the pre-implementation or post-implementation periods (target n=48, three patients per cluster per time period) will be invited to participate in semi-structured interviews to explore changing perceptions of clinic experiences over time. Focus groups and interviews will be facilitated by members of the research team with experience in qualitative research methodology and will be recorded and transcribed. Participants will be provided with a copy of transcripts from interviews/focus groups and invited to provide comments or additional contributions (member checking). Written informed consent will be obtained from all focus group and interview participants (online supplemental file B).

#### Health economics data

During the 27-month study period, data for the cost of implementation analysis will be obtained from the following sources: (i) data extracts from clinic administrative and waiting list databases, (ii) audit of patient medical records and (iii) verbal reports obtained from clinic leaders through direct approach and semi-structured interviews. This costing data will be prospectively collected using a customised Excel spreadsheet at the end of each 3-month period (online supplemental file A details the data fields). The spreadsheet will capture 6-month pre-implementation, 6-month implementation and 6-month post-implementation of the STAT model (see figure 1). Cost-effectiveness analysis will include the cost of implementation data, as well as individual participant health service utilisation data, to determine the cost and tracking of patient waiting times to determine the effect.

### Outcome measures

#### Effectiveness outcomes

Quantitative outcomes will be obtained from routinely collected healthcare data and auditing of health service processes. The primary outcome measure for effectiveness will be waiting, measured as time from initial referral to first appointment and the number of people on the waiting list (measured weekly). Secondary outcomes include the number of emergency department presentations and days admitted to the health service during the 6 months prior to and following the first clinic assessment to determine whether there is a relationship between improved specialist clinic access and other health service utilisation (outpatient services, emergency presentations and health service admissions). These data will be collected for a subgroup of patients attending the clinic for the first time within two of the pre- and post-implementation time blocks (darker shades in figure 1). Factors that may be covariates that impact on waiting times will also be recorded (demographic data, diagnosis and referral source).

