The stepped wedge cluster randomised controlled trial (figure 1) will sequentially introduce the STAT intervention to clinics provided within eight speciality areas (clusters) in random order. Control data will be collected for 6 months (commencing 31 March 2025), after which the STAT model strategies will be introduced sequentially to two clusters within each step, with new steps commencing at 3-month intervals. There will be a 6-month period for implementation at each cluster, followed by commencement of collection of post-implementation data. The post-intervention data collection period for all clusters will conclude on 27 June 2027. While the design carries some risk of contamination and implementation fatigue due to the possibility of some of the same staff working across different clusters, this will be minimised through the inclusion of a diverse range of clinical specialties and a structured implementation process supported by project staff. Data will be collected for at least 6-month post-implementation at all clusters (figure 1). The primary effectiveness outcome will be a comparison of waiting (measured as time to first appointment and number of people on the waiting list) across the pre- and post-implementation periods. Implementation outcomes will be organised under six domains of acceptability, adoption, appropriateness, feasibility, fidelity and costs using a mixed-methods approach incorporating qualitative data and routinely collected healthcare data.

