### Randomisation and masking

The eight clusters will be randomly paired, and then the four pairs will be randomised for order of intervention. Randomisation will be undertaken using a random number sequence, computer-generated by an external clinical trial support service not involved in the study and blind to the identity of the participating medical specialties. Researchers and participants will not be informed which clusters will form the next intervention pair until 3 months prior to commencement of their implementation period. Clinic patients will not be aware of the study, and routinely collected data contributing to the primary outcome measure (referral and appointment dates used to calculate waiting time, patients allocated to the waiting list) are collected by a centralised data management service within the health organisation independent from the research team. Patients attending the service and the health service staff collecting the primary outcome can therefore be considered blinded to the intervention.

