### Intervention and implementation strategy

The intervention will consist of a suite of service redesign initiatives based on the STAT model. During the implementation period, staff within each cluster will be trained in the STAT model in workshops of 1–4-hour duration (tailored for teams and individuals according to prior knowledge of STAT and role within the service, with options for flexible delivery), led by investigators [name] and [name]. This training was developed at Eastern Health/La Trobe University and has been delivered to more than 1000 clinicians across Australia from more than 100 services over the past 4 years.^35^

Following training, the clinic staff will be guided through each of five steps of the STAT model: (i) analyse clinic supply and demand data, (ii) model supply and demand at the clinic, (iii) targeted interventions to address the existing backlog (using a comprehensive waiting list audit supplemented by targeted, short-term supply-side interventions), (iv) protect capacity for new patients to align with demand and (v) implement tailored strategies to enhance patient flow. Step 5 will incorporate enhanced clinic coordination, alongside other strategies that could include (but are not limited to) productivity improvements (such as reducing failure-to-attend rates), multi-disciplinary approaches to service delivery and partnerships with patients and primary care (table 1).

**Table 1 T1:** Key WaitLESS intervention activities and corresponding resources

Key activities	Resources provided
**Staff training** in the principles of the STAT model	Four-hour workshop training provided by members of the research team
**STAT Step 1:** Retrospective collection and analysis of clinic data—typical supply and demand over past 2 years	Support from research team/project manager
**STAT Step 2:** Model supply and demand; determine how much capacity needs to be protected for new patients to maintain flow at the rate of demand	Support from research team/project manager
**STAT Step 3**: Address existing backlog. Example activities: Comprehensive waitlist audit: cleaning the list, including checking for errors and calling/messaging patients to determine need Short-term increase in supply Grouping similar patients for targeted interventions	Clerical assistance for auditing Some funding for additional short-term clinic supply
**STAT Step 4:** Redesign clinic templates to align with demand	Support from research team/project manager

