#### Implementation outcomes

Implementation measures are organised using the taxonomy of Proctor and colleagues, who described eight outcome measures for implementation research: acceptability, adoption, appropriateness, costs, feasibility, fidelity, penetration and sustainability.^37^ The current study includes measures within the first six of these outcome domains, acknowledging that the timelines planned for the current trial are likely to be insufficient to obtain a robust assessment of penetration and sustainability. These outcomes will be addressed in future studies.

Adoption outcomes will evaluate whether ‘action steps’ of the model have been implemented: targeted strategies to reduce the backlog of waiting patients, protected capacity for new patients based on demand and changes to models of care to enhance flow. Descriptions of backlog strategies and model of care changes will be obtained through staff focus groups and interviews with patients. The ratio of the number of new patients in the template to referrals received in the pre- and post-implementation periods will be used to determine whether clinics protected capacity to align with predicted demand.

Fidelity of the STAT model will be evaluated by measuring how well these action steps were completed. The outcomes of the backlog reduction process will be described using audit data (including the number of patients removed from this list and reasons why and the number scheduled for care). The average number of new referrals accepted and booked into appointments each week will be used to determine how well the clinics are able to align supply and demand in the pre- and post-implementation periods. Outcomes indicative of changes to models of care delivery at each cluster will be compared pre- and post-intervention, including: mode of care delivery (telehealth/face to face, type of practitioner), appointment outcomes (proportion discharged or booked for review), failure to attend rates, clinical patient contacts outside clinic times (eg, telephone follow-up, calls seeking advice) and the ratio of new to review patients in clinic schedules.

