**Fidelity**				
Descriptive analysis of backlog reduction activity				
Number of patients removed from list				✓
Reasons for removal (appointment previously provided, service not needed, unable to contact)				✓
Number of patients scheduled for care				✓
Ratio of expected demand to new patient appointments booked	✓			
Indicators of change in care delivery				
Mode of delivery (face to face, telehealth)	✓			
Number of appointments scheduled by professional type (medical, nurse, allied health)				
Appointment outcomes (proportion rebooked/discharged)	✓			
Attendance (expressed as proportion failed to attend)	✓			
Ratio of new to review patients scheduled	✓			
Contacts with clinic staff outside of the allocated clinic appointments (eg, telephone advice and follow-up)				✓

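### The weekly waiting-list count comes from a record that STAT's own audit cleans, so part of any estimated fall may be record correction

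*Protocol article*

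**What the plan says.** The Design section of the protocol article describes the primary effectiveness outcome as a "comparison of waiting (measured as time to first appointment and number of people on the waiting list) across the pre- and post-implementation periods". The Effectiveness outcomes section repeats list size as part of the primary measure, "the number of people on the waiting list (measured weekly", and Table 3 lists it under primary outcomes with routine data as its only ticked source. The Randomisation and masking section treats the "routinely collected data contributing to the primary outcome measure" as independent of the research team because a central service collects them.

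Under Intervention and implementation strategy, Step 3 tackles the backlog "using a comprehensive waiting list audit supplemented by targeted, short-term supply-side interventions". Table 1 gives the audit's content: "Comprehensive waitlist audit: cleaning the list, including checking for errors and calling/messaging patients to determine need". On timing, the Design section says: "There will be a 6-month period for implementation at each cluster, followed by commencement of collection of post-implementation data".

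Table 3 places removal counts and reasons under Fidelity, sourced from prospective audits: "Reasons for removal (appointment previously provided, service not needed, unable to contact". The Implementation outcomes section says: "The outcomes of the backlog reduction process will be described using audit data". The Analysis section treats the audit results descriptively. For the primary outcome it specifies linear mixed models with time-point and time since intervention as factors, and it does not link the audit removals to that analysis.

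**The concern.** A person who has already had an appointment but is still listed is not waiting. That entry is counted in every control week until the audit and in no week after it. The article describes cleaning only as part of STAT, so the recorded list carries more of this error before a cluster crosses over than after.

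The planned model cannot separate the two. The time-point factor absorbs changes common to all clusters at one calendar time. The cleaning follows each cluster's own crossover, so it loads on time since intervention, together with any real fall in people waiting. Independent extraction does not help either, because the intervention alters the source record before the count is taken.

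The trial asks whether STAT shortens waiting lists as well as waiting times. A recorded list can shrink with nobody seen sooner, and a reader of the list-size estimate could not tell. The same applies to the backlog cost in the Analysis section, whose divisor is the change in list size, so corrected records would count there as backlog cleared.

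**Working it through.** The article gives no effect size, power figure or error rate for list size, so there is no stated figure to reproduce. What follows is illustrative.

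**Inputs**
- L, recorded list before the audit: 200 (the eligibility threshold under Inclusion criteria) or 600 (the pilot clinic's list in the Introduction).
- r, share of recorded entries that are record errors: not in the article; assumed 5%, 10%, 20% or 30%.
- d, true proportional fall in people waiting: 0, 10%, or 34%. The last is borrowed from the earlier STAT trial's waiting-time result in the Introduction. It is not a list-size effect.
- Assumption on timing: the audit is finished within the implementation period, so post-implementation counts come from audited lists.

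**Errors all removed and none returning**

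Recorded list afterwards = L(1 − r)(1 − d). Apparent fall = 1 − (1 − r)(1 − d) = r + d(1 − r). Share of that fall due to record correction = r / [r + d(1 − r)].

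| r | d = 0: list of 200 becomes | d = 0: list of 600 loses | d = 10%: apparent fall (record share) | d = 34%: apparent fall (record share) |
|---|---|---|---|---|
| 5% | 190 | 30 | 14.5% (34%) | 37.3% (13%) |
| 10% | 180 | 60 | 19% (53%) | 40.6% (25%) |
| 20% | 160 | 120 | 28% (71%) | 47.2% (42%) |
| 30% | 140 | 180 | 37% (81%) | 53.8% (56%) |

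Example: r = 10%, d = 10% gives 1 − 0.90 × 0.90 = 0.19, and 0.10/0.19 = 53%.

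**Errors building up again after the audit**

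Let T = L(1 − r) be the true waiters before STAT, and let k be the fraction of the original number of errors present again in a typical post-implementation week.
- True fall: Td.
- Raw fall: L − [T(1 − d) + krL] = Td + (1 − k)rL.
- Fall if only control weeks are corrected: T − [T(1 − d) + krL] = Td − krL.

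For k between 0 and 1, the raw count overstates the true fall by (1 − k)rL, and a one-sided correction understates it by krL. With L = 200, r = 10%, d = 10% and k = 0.5 (assumed), T = 180. The true fall is 18, the raw fall is 18 + 10 = 28, and the one-sided corrected fall is 18 − 10 = 8. The two estimates bracket the truth. Only a check applied to both periods recovers it.

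**The case against.** The strongest reply is that the audit is treatment and not measurement. It is a named part of Step 3, and the article costs backlog reduction, auditing included, per patient removed from the list. A fall in the recorded list caused by the audit is then a real effect of STAT on the stated outcome, and the model rightly credits it to STAT. This stands to a large extent. It is why the raw count should stay, and why removals of people who no longer need the service, or who cannot be reached, should be shown as an intended effect. It does not cover entries for people already given an appointment. Removing those changes the record and leaves the number waiting as it was.

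Second, the abstract names time from referral to first appointment as the primary effectiveness outcome, and the trial is powered on it. A removed entry yields no first appointment, so that measure is not directly inflated. This also stands, and it limits the point to list size.

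Third, derivation rules may sit in an analysis plan or in the supplementary data-field list, neither of which is shown. That is possible. But the article itself assigns removal reasons to descriptive fidelity reporting and gives list size a routine-data source only, and that stated allocation is what needs changing.

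A reader might go further and infer that the list-size effect is mostly artefact, or that a back-corrected count should replace the raw one as the primary outcome. The article supports neither. It gives no error rate, it does not define the already-provided category, and the figures above only return the r that is put in. It describes no second audit of post-implementation lists, so correcting control weeks alone would turn the differential error against STAT. Dates set by the audit team would also come from inside the intervention.

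**Conclusion.** The point holds for one primary outcome, and it concerns what that outcome means. Control weeks count entries that the intervention's own audit is expected to delete as not waiting, and the planned model credits the deletion to STAT. The direction favours STAT as long as fewer such errors are present after the audit than before it (k below 1).

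The amount cannot be derived. Under the assumed 5% to 30% of invalid entries, cleaning alone produces an apparent fall of 5% to 30%. If the true fall were 10%, between 34% and 81% of the recorded drop would be record correction. These ranges rest on r, on the audit finding every error, and on no new errors appearing.

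The trial remains valid and the raw count is a legitimate measure of the recorded list. On its own, however, a raw fall does not show improved access, and the plan should provide the analysis that tells the two apart.

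**What to change.** Keep the raw weekly count as the planned outcome and prespecify the following beside it.

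1. **Corrected series, same mixed model.** Take entries removed because an appointment had already been provided, duplicates and other clear record errors out of earlier weekly counts. Start from the date shown in the centrally held appointment or referral record, not a date assigned by the audit team.
2. **Same check after implementation.** Search post-implementation weeks for people already seen but still listed, so that both periods are counted alike. If this cannot be done, present the raw and corrected estimates as bounds.
3. **Other removals.** Report the part of the fall due to people no longer needing the service, or not reachable, separately as an intended part of STAT.
4. **Interpretation.** State that the raw fall alone will not be read as improved access.

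Removal reasons are already to be collected and appointment dates are already held, so the added cost is linking each error removal to its list record and re-deriving the weekly series. The link should be captured while the audits are run. The downsides are a possibly smaller apparent effect, and some errors that cannot be dated and so stay in the early counts.

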**Trial registration number:**

ISRCTN15820171.

STRENGTHS AND LIMITATIONS OF THIS STUDYRobust design, using a stepped wedge cluster randomised controlled trial to test a service-level intervention to reduce waiting times in specialist medical outpatient services.Inclusion of implementation outcomes and a health economics analysis will provide valuable insights into how the model is implemented, reasons for success or failure, costs of implementation and cost-effectiveness.The intervention (the Specific Timely Assessment and Triage (STAT) model) brings together evidence-based principles into one structured, step-by-step package that is described using the Template for Intervention Description and Replication checklist for future replication.Lack of direct measurement of individual patient health outcomes could be considered a limitation. However, we will capture qualitative data on patient experience as well as health service use during the periods before and after the index outpatient appointment as a proxy indicator of changes in health status.

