## Method

### Setting

The trial will take place at Eastern Health, a large network of metropolitan services in the eastern suburbs of Melbourne, Australia, providing publicly funded health services to a diverse community of approximately 892 000 people, including a high proportion (32%) of residents born overseas. Eastern Health offers a broad range of services, including emergency care, surgery, maternity, palliative care, mental health, drug and alcohol services, residential care and community health, delivered across three tertiary hospitals, two sub-acute inpatient services, a small community hospital, a day surgery centre and more than 30 community sites. The inclusion of a single health service could be seen as a limitation, but the size of the health network and its operation across multiple sites spanning a diverse geographical catchment provide confidence in the applicability of the findings to a broad range of health settings.

Eastern Health operates a comprehensive network of specialist medical clinics, providing expert care across a broad range of medical disciplines. Patients are typically referred to these clinics by general practitioners, specialists or hospital-based clinicians. Referrals are made electronically, then triaged by clinicians and assigned a priority category. Urgent referrals may be booked directly into appointments, while routine referrals are waitlisted until an appointment becomes available. Waiting times vary from weeks or months to several years.

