Acceptability, feasibility and appropriateness will be evaluated using qualitative data from staff and patients. Staff perspectives will be sought during the pre-implementation and implementation periods (perceptions of current state, views about the intervention and challenges/enablers for implementation) as well as 6 months after the commencement of the post-implementation period (perceived success or failure of the intervention, impact on patient care, staff workloads and job satisfaction and reflections on feasibility and appropriateness of the STAT model for specialist clinics). Patient perspectives of the clinic service will be sought from samples of patients who attend during the pre- and post-implementation periods.

The total cost of implementation will be considered in two parts: (i) Cost of initial backlog reduction (auditing and short-term additional supply) per patient removed from the waiting list and (ii) total cost of clinic operations during the pre- and post-implementation periods. The cost-effectiveness of the STAT programme will determine the incremental cost per percentage of urgent referrals seen within 30 days and routine referrals seen within 90 days, comparing usual care conditions to intervention conditions. Individual patient health service utilisation cost (outpatient services, emergency presentations and health service admissions) will be collected for the 6 months prior to their first clinic appointment and the first 6 months following this appointment, for patients under usual care conditions and for patients under intervention conditions (estimated n=800).

Outcome measures across all aspects of the trial are summarised in table 3.

**Table 3 T3:** Summary of outcome measures and data sources

	Routinely collected data	Consumer interviews	Staff focus groups	Prospective audits

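### Health service use and its cost are counted around the first appointment, whose date the intervention is meant to move, so the two conditions are compared at different times since referral

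*Protocol article*

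**What the plan says.** Under Effectiveness outcomes, the secondary outcome is emergency presentations and days admitted "during the 6 months prior to and following the first clinic assessment". Its stated purpose is "to determine whether there is a relationship between improved specialist clinic access and other health service utilisation". The data come from "a subgroup of patients attending the clinic for the first time within two of the pre- and post-implementation time blocks", so patients enter by attendance.

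Under Implementation outcomes, the cost of each patient's outpatient, emergency and inpatient use "will be collected for the 6 months prior to their first clinic appointment and the first 6 months following this appointment", and usual-care patients are compared with intervention patients, about 800 in all. Health economics data places this in the cost-effectiveness analysis.

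The strengths and limitations list concedes that patient health outcomes are not measured directly, and offers "health service use during the periods before and after the index outpatient appointment as a proxy indicator of changes in health status".

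The primary outcome is the time from referral to that same first appointment. Setting says that waits range from weeks to several years and that "Patients are typically referred to these clinics by general practitioners, specialists or hospital-based clinicians". The article describes no window that starts at referral.

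**The concern.** A comparison of event counts needs a time zero that the intervention cannot move. Here time zero is the first appointment, and moving it is what STAT is for. Two things follow.

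- **Lost benefit.** One route by which faster access could reduce hospital use is that patients spend less time waiting untreated. Windows of fixed length around the appointment largely hold the mix of waiting and post-appointment time constant, so this saving may not appear.
- **Created difference.** A STAT patient is seen earlier after referral than a control patient. If use changes with time since referral, counts differ even when STAT has no effect on use. If the STAT wait is under 6 months and the control wait is longer, the STAT pre-window also reaches back before referral and can take in the event that prompted it.

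At stake are the trial's quantitative proxy for health status and the patient-level part of the cost difference in the cost-effectiveness analysis.

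**Working it through.** The article states no rate, effect size or power for utilisation, so there is no figure of its own to reproduce. The check is window arithmetic.

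**Inputs from the article.** Windows are 6 months each side of the appointment. Clusters may enter with an average wait of 12 weeks, about 2.8 months (Inclusion criteria). Nationally, half of patients wait over 50 days and 10% over a year (Introduction). The earlier STAT trial cut waits by 34%, a ratio of 0.66 (Introduction).

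**Assumed.** Rates per patient-month are 0.10 events while waiting, 0.05 after the appointment, and 0.05 or 0.10 before referral. Most wait pairs apply the 0.66 ratio, rounded (12 × 0.66 = 7.9); the pairs ending in 3 months show a larger reduction.

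**Step 1: waiting time captured.** Let W and w be the control and STAT waits in months from referral. The windows span W − 6 to W + 6 and w − 6 to w + 6. Waiting months in the pre-window are min(W, 6) and min(w, 6). The share of removed waiting time that appears in the contrast is [min(W, 6) − min(w, 6)] / (W − w).

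**Step 2: events.** Both post-windows contribute 6 × 0.05 and cancel. With p the pre-referral rate, the STAT-minus-control difference over the 12 months is −[min(W, 6) − min(w, 6)] × (0.10 − p). Counted from referral over 30 months it is −(W − w) × (0.10 − 0.05), whatever p is.

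| W v w | Months removed | Waiting months in pre-window | Share captured | Appointment windows, p = 0.05 | Appointment windows, p = 0.10 | From referral, 30 months |
|---|---|---|---|---|---|---|
| 5 v 3.3 | 1.7 | 5 v 3.3 | 100% | −0.085 | 0 | −0.085 |
| 9 v 6 | 3 | 6 v 6 | 0% | 0 | 0 | −0.150 |
| 12 v 7.9 | 4.1 | 6 v 6 | 0% | 0 | 0 | −0.205 |
| 12 v 3 | 9 | 6 v 3 | 33% | −0.150 | 0 | −0.450 |
| 24 v 16 | 8 | 6 v 6 | 0% | 0 | 0 | −0.400 |

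For 24 v 3 months the share captured is 3 / 21 = 14%.

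**Step 3: difference with no effect on use.** Suppose use declines after referral as 0.1 × exp(−t/12) per month in both conditions. The STAT/control ratio in the post-window is then exp[(W − w)/12]: 1.15 for 5 v 3.3, 1.28 for 9 v 6, 1.41 for 12 v 7.9 and 2.12 for 12 v 3. The anchor alone produces these.

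**Step 4: referral-triggering admissions.** Suppose a share of patients had a 4-day stay in the month before referral. Where W is at least 6 and w is at most 5, that stay falls in the STAT pre-window and not in the control one. The artefact is share × 4: 0.4, 1.2 or 2.0 bed days at 10%, 30% or 50%. If both waits are under about 5 months it falls in both windows; if both exceed 6, in neither. The extra days raise STAT's total use but make its before-after change look better, so the direction depends on the contrast.

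**The case against.** A reader might infer that use avoided while waiting is never observed. The documents do not support that. A control wait of up to 6 months, which the 12-week entry criterion allows, lies wholly in the pre-window. For longer waits the last 6 months are still recorded. What fails is the alignment of the two conditions.

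A reader might also infer that referral-triggering admissions enter only the STAT window and make STAT look harmful. Step 4 shows that this needs a particular pairing of waits. Referral source is also recorded and named as a model covariate, which addresses part of the problem. Nor does a fall from 12 to 3 months by itself give equal counts: that requires pre-referral use equal to use while waiting, an assumption incompatible with a surge of admissions just before referral.

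The other side has further points that stand. The stated aim is a relationship between access and utilisation, not total use avoided, and use in the 6 months after being seen is a legitimate question. A referral anchor has costs too. Long waiters' windows fall in earlier calendar time, some contain no post-appointment care, and with data collection ending on 27 June 2027 a full 12 months is observable by then only for referrals up to about June 2026. Truncation is not peculiar to the referral anchor, though: a patient first seen after about 27 December 2026 also lacks a full 6 months after the visit by that date.

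None of this realigns the comparison. Terms for calendar time and time since intervention do not adjust for time since referral.

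**Conclusion.** The point holds in limited form. As written, the plan compares usual-care and STAT patients at different times since referral in a secondary outcome and in patient-level costs. Savings from a shorter wait cancel when both waits are 6 months or longer. With shorter waits, capture runs from none to all, depending on the two waits and the pre-referral rate. Spurious differences can arise in either direction.

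The waiting months captured follow from the stated windows once the waits are given. The event counts, ratios and bed days rest on assumed rates. The article gives neither utilisation rates nor the distribution of waits in the included clusters, so how often each case applies is unknown. Waiting time, waiting-list size and the effect side of the cost-effectiveness ratio (the percentages seen within 30 and 90 days) are unaffected. This should be corrected before utilisation is read as evidence of benefit or harm, but it does not threaten the main result.

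**What to change.** Add a count of emergency presentations, bed days, outpatient use and cost from the day after referral over a fixed horizon that is the same in both conditions: for example 6 months, and 12 months where observable. Use observed time as an offset in the negative binomial model for the counts. Base any statement about the intervention's effect on utilisation or patient-level cost on this count. Report the appointment-centred windows as a description of use around the visit.

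The horizon matters. Over H months from referral, the waiting months that differ are min(W, H) − min(w, H). For 12 v 7.9 months this is 0 at H = 6 and 4.1 at H = 12; for 24 v 16 it is 0 at both. The 6-month count is a fair comparison of the first 6 months, but only a longer horizon can show savings made later, and this limit should be stated.

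Assign condition by referral date. If sampling stays by attendance, adjust for the calendar time of the counted window and report the limitation.

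The cost is protocol wording and a wider date range in the routine-data extract; referral dates are already collected. The downsides to state are that long waiters need records back to referral, their horizon may hold no post-appointment time and falls in earlier calendar time, and late referrals have truncated follow-up.
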